### Outcomes measures

As shown in Fig. 2, outcome assessment at baseline, 6,12, 18 and 24 months: bloods and self-report outcomes will be collected by trial staff. Biometric measures constitute total and high cholesterol lipids, blood pressure, weight in kilogrammes, blood glucose level, height and waist measurement in centimetres, %COHb, blood COppm, which constitute the necessary information to calculate the General CVD Risk Score [31]. The self-report measures comprise quality of life [32] SF-12; psychological distress [33] K-10; the Alcohol Use Disorders Identification Test - consumption [34] AUDIT C-3; the Fagerström Test for Nicotine Dependence [35]; the Medical Outcomes Study Sleep measure [36] MOS Sleep; International Physical Activity Questionnaire [37] IPAQ; Australian dietary guidelines healthy eating quiz [38], Partners in Health [39, 40] PIH; Patient Assessment of Chronic Illness Care [41] PACIC; Singh O’Brien Level of Engagement Scale [42] SOLES. Hospital admissions will be extracted from service records to minimise burden on patients and health care staff.

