### Statistical analysis

Data analyses will be undertaken using an *intention-to-treat* methodology, adhering to CONSORT guidelines. However, where necessary, analyses will also adopt a *per protocol* approach. The following processes have informed the sample size calculation for the 10-year CVD risk change score. Our pilot data (*n* = 17) found mean (SD) of 10-year risk to be 16.9% (9.8%). Thus, taking a conservative baseline mean CVD risk score of 10.5% and a proportionate SD of 6% and assuming a correlation of 0.5 between baseline and follow up scores, a sample of 304 (i.e., 152 per group), provides 80% power to detect a relative change of 20% in 10-year CVD risk. This calculation was achieved using Stata’s *sampsi* command. These changes are realistic; other current empirically-designed interventions providing coordination alone [44, 45] or self-management alone [46, 47] have achieved substantial levels of change. If necessary, we will transform non-normal data to meet normality conditions. The present intervention provides *both* coordination and self-management, and also includes management of CVD risk. We will sample a total of 358 participants allowing for an attrition rate of 15%. Linear regression will be employed to analyse primary outcomes, clustering over nurse delivering the intervention to account for possible correlated outcome measures. The dependent variable will be the outcome at follow-up. The independent variables will be the outcome at baseline and group assignment. Diagnostic tests to examine homoscedasticity and normality of residuals will be carried out to ensure model validity. The calculations for each primary outcome assume a Type I error rate of 2.5% to protect the overall Type I error rate of 5%. A three level random effects mixed models, using Stata’s *mixed* command will be used to analyse outcomes at several timepoints. If necessary, time will be reparametrised. Nurse, and individual within nurse, will be entered as random effects to account for correlated measures within an individual. The dependent variable will be the outcome at each timepoint. The independent variables will be group assignment, time and the product term group ‘x’ time. Differences between groups across time will be assessed via the interaction term. All results will be reported with 95% confidence intervals, and a *p*-value of less than 0.05 (two-tailed) will be deemed to be statistically significant. All analyses will use Stata (StataCorp, College Station, Texas).

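### On its natural reading the repeated-measures model holds within-person correlation constant over 24 months; if correlation fades and time is linear, the group-by-time test runs at about 6% to 20% instead of 5%

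*Protocol article*

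**What the plan says.** All of this stands in the protocol article. No separate analysis plan is at hand.

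- Model (Statistical analysis): "A three level random effects mixed models, using Stata’s *mixed* command will be used to analyse outcomes at several timepoints".
- Within-person correlation (same section): "Nurse, and individual within nurse, will be entered as random effects to account for correlated measures within an individual". No random slope, residual correlation structure or robust standard error is named for this model.
- Fixed effects: "The independent variables will be group assignment, time and the product term group ‘x’ time".
- Test: "Differences between groups across time will be assessed via the interaction term", with "a *p*-value of less than 0.05 (two-tailed) will be deemed to be statistically significant".
- Form of time: not fixed. The only remark is "If necessary, time will be reparametrised".
- Visits (Outcomes measures): "outcome assessment at baseline, 6,12, 18 and 24 months", so five occasions.

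The same section assigns the primary outcomes to a different analysis, a linear regression of the follow-up value on the baseline value and group.

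**The concern.** In Stata's `mixed`, naming only the levels gives a random intercept at each level and independent residuals. Two visits by the same person then have the same correlation whether they lie 6 or 24 months apart, and every person's underlying trajectory is parallel to everyone else's. Any real difference between people in drift is treated as independent visit noise. A slope comparison between arms rests on exactly that variation, so its standard error comes out too small. The test can then reject because individuals drift apart, not because the arms do.

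Fading correlation is plausible here, though not shown. The CVD score includes yes/no items for smoking, diabetes and blood-pressure medication, and a change in one of these can persist in one person and not in another.

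At stake is the only stated test across all the follow-up times. A standard error that is too small could support a claim of sustained benefit over two years that the data do not carry.

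**Working it through.** **Inputs from the protocol article.** Five visits; SD 6 points; a correlation of 0.5 between baseline and follow-up with no lag; 152 per group, 358 in total after 15% attrition; two-sided 5%.

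**The plan's own figure.** The plan gives no operating characteristic for the interaction test. Its sample size shows how the 0.5 is used. The SD of change is 6 × √(2 × (1 − 0.5)) = 6 and the difference is 20% of 10.5 = 2.1. At two-sided 2.5% and 80% power, n = 2 × 6² × (2.241 + 0.842)² / 2.1² ≈ 155.2, so 156 per group and 312 in total. That is within 3% of the stated 304, and power at 152 per group is 79.1%. Attrition: 304 / 0.85 = 357.6, so 358. The 0.5 is thus a single baseline-to-follow-up value and says nothing about how correlation behaves over time.

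**Assumptions added here.** Linear time, no true effect, equal variance at each visit, nurse level omitted, complete data. The correlations are varied.

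**Formulas** (variances in units of SD² = 36). Under a random-intercept fit to balanced data, the group-by-time estimate is the difference in mean within-person least-squares slopes. Let r6, r12, r18, r24 be the correlations at those separations and c = (−2, −1, 0, 1, 2), so Σc² = 10.

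- Variance the model reports, per person: s²/10, with s² = 1 − (4r6 + 3r12 + 2r18 + r24)/10.
- True variance, per person: c′Vc/100, with c′Vc = 10 + 8r6 − 2r12 − 8r18 − 8r24.
- Ratio R = (c′Vc/100) / (s²/10); type I error = 2 × (1 − Φ(1.96/√R)).

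| r6, r12, r18, r24 | s² | c′Vc | R | Type I error |
|---|---|---|---|---|
| 0.50, 0.50, 0.50, 0.50 | 0.500 | 5.00 | 1.00 | 5.0% |
| 0.55, 0.533, 0.517, 0.50 | 0.467 | 5.20 | 1.11 | 6.3% |
| 0.55, 0.50, 0.475, 0.45 | 0.490 | 6.00 | 1.22 | 7.7% |
| 0.60, 0.50, 0.45, 0.40 | 0.480 | 7.00 | 1.46 | 10.5% |
| 0.60, 0.50, 0.40, 0.30 | 0.500 | 8.20 | 1.64 | 12.6% |
| 0.50, 0.25, 0.125, 0.0625 (exponential, 0.5 at 6 months) | 0.694 | 12.00 | 1.73 | 13.6% |
| 0.707, 0.50, 0.354, 0.25 (exponential, 0.5 at 12 months) | 0.471 | 9.83 | 2.08 | 17.5% |
| 0.841, 0.707, 0.595, 0.50 (exponential, 0.5 at 24 months) | 0.283 | 6.56 | 2.32 | 19.8% |

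Sample size cancels out of R, so recruiting more participants does not help.

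**Person-specific slopes.** Add slope variance v per visit² to constant correlation 0.5. Then R = (0.05 + v) / ((2 + 10v)/40). For a slope SD of 0.15 baseline SDs per visit (0.9 points per 6 months), v = 0.0225 and R = 0.0725/0.0556 = 1.30, giving 8.6%. For 0.20 (1.2 points), v = 0.04 and R = 0.09/0.06 = 1.50, giving 11.0%.

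**Time as visit categories.** Over the fading patterns examined, the joint 4-df test runs at 5.0% to 7.6%. The 24-month-versus-baseline contrast alone runs at 5.8% to 14.1%. For example, under exponential decay with 0.5 at 12 months, R = 2(1 − 0.25)/(2 × 0.471) = 1.59, giving 12.0%. The 6-month contrast errs the other way, at 0.9% to 4.6%.

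**Simulation check.** With 358 participants, 15% dropout by 24 months, the random-intercept model fitted by maximum likelihood and 1,000 runs per pattern:

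| True correlation | Linear time | Categories, joint test |
|---|---|---|
| Constant 0.5 | 4.3% | 5.9% |
| Exponential, 0.5 at 6 months | 14.0% | 6.8% |
| Exponential, 0.5 at 12 months | 18.0% | 7.4% |
| Exponential, 0.5 at 24 months | 19.8% | 8.0% |

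The Monte Carlo standard error is about 0.7 points at 5% and 1.2 points at 18%, so the simulation agrees with the formulas.

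**The case against.** The strongest reply is that within-person covariance is ordinary analysis-plan detail, that the source is a condensed article, and that nothing in it forbids a random slope or a residual structure. That is right as far as it goes. A reader might infer that the plan commits to random intercepts only. It does not say so; this is the natural reading, not a stated decision. The point still stands, because the article is not silent: it names the device meant to handle within-person correlation, and that device, used as described, is insufficient when correlation fades.

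Second, linear time is not stated. A single product term points towards it, but the remark on reparametrising time leaves visit categories open. With those and a joint test, most of the inflation disappears. This also stands, and it is why the size must be given conditionally.

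Third, fading is assumed. With constant correlation the test runs at exactly 5.0%. This stands too.

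A reader might also infer a general doubling or tripling of false positives. The figures do not support that. Under linear time the factor runs from about 1.3 to 4 depending on the assumed fading, and with a joint categorical test it is at most about 1.6.

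**Conclusion.** The point holds in conditional form. As described, and read as random intercepts with independent residuals, the longitudinal model can give standard errors that are too small for the group-by-time test. With linear time the type I error is about 6% to 20% against a nominal 5%: about 8% to 13% for gentle to moderate fading, and 17.5% for exponential decay with 0.5 at 12 months. With visit categories and a joint test it is about 5% to 8%, with a possible excess in a 24-month contrast taken alone. The result rests on three things that the protocol does not fix: intercepts only, linear time, and correlation that fades or slopes that differ between people.

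It would be tempting to conclude that the trial's primary comparison is compromised. The document does not support that. The primary outcomes have their own baseline-adjusted linear regression, which does not use this covariance. The exposure is confined to the repeated-measures analysis, and the change is a cheap improvement.

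**What to change.** Keep the mixed model, but give participants an unstructured residual covariance over the five visits. In Stata the participant level becomes `|| id:, noconstant residuals(unstructured, t(visit))`, placed after whatever nurse term is retained. If that does not converge, use a participant random intercept plus random slope for time with unstructured covariance. State in advance whether time is linear or categorical and, if categorical, whether the test is joint or a named contrast.

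The cost is a sentence or two of analysis wording and a different option in the same command, with no new data or participants. The model carries 5 × 6/2 = 15 covariance parameters within participant in place of two, which about 300 participants can support. Intervals for the interaction may be somewhat wider. For the four fading patterns with 0.5 at 12 months, the current standard error is too small by a factor of √R, that is 1.11 to 1.44. If correlation is in fact constant, little is lost.

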**Fig. 2 Fig2:**
[figure not shown]
Standard Protocol Items: Recommendations for Interventional Trials (SPIRIT) Figure of enrolment, treatment and assessments over time

Key outcomes will involve assessing change at 6, 12, 18 and 24 months for the following measures:Absolute CVD risk will be measured using the General CVD Risk Score [31]. This measure applies from age 30 years and includes gender, age, systolic blood pressure, smoking in last week (Y/N), diabetes (Y/N), hypertensive medication (Y/N), and either total and HDL cholesterol or body mass index (Aim 1, Hypothesis 1).Health-related quality of life will be measured by the SF-12 [32], a validated and commonly used instrument, producing summary scores for mental health and physical health components. The Australian SF-6D scoring algorithm developed by [name] and colleagues will be applied to generate utilities and calculate quality adjusted life years [43], (Aim 1, Hypotheses 2 and 3).

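### The longitudinal mixed model makes no baseline adjustment, so its group-by-time test is less precise than it need be or, if only months 6 to 24 are modelled, tests the wrong contrast

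*Protocol article*

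**What the plan says.** All places are in the protocol article, under Methods/Design.

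- **Single-timepoint model (Statistical analysis).** The primary outcomes are analysed by linear regression of the follow-up value: "The independent variables will be the outcome at baseline and group assignment".
- **Longitudinal model (same section).** Outcomes at several timepoints go into a three-level mixed model with random effects for nurse and for individual within nurse. Its fixed part is: "The independent variables will be group assignment, time and the product term group ‘x’ time". Group differences over time are judged by the interaction. There is no baseline covariate and no constraint that the arms share a baseline mean. The text does not say whether baseline is one of the modelled timepoints, and it allows time to be recoded if needed.
- **Visits (Outcomes measures).** Assessments are at baseline and at months 6, 12, 18 and 24. "Key outcomes will involve assessing change at 6, 12, 18 and 24 months for the following measures": the General CVD Risk Score and the SF-12.
- **Timing of baseline (Trial procedures; Randomisation and blinding).** Baseline data are collected before allocation, which is 1:1 and stratified by median age and gender.

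**The concern.** The two models treat the baseline value of the same outcomes differently. Baseline is measured in everyone before allocation, so it is available to both models at no cost.

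The mixed model can be read in two ways, and neither serves the trial well.

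1. **Baseline is a modelled timepoint.** The free group term then estimates a baseline difference between arms that randomisation makes zero in expectation. With categorical time, the interaction term for a visit is the difference between arms in raw change from baseline. Its variance is proportional to 2(1 − ρ), where a baseline-adjusted contrast has 1 − ρ².
2. **Only months 6 to 24 are modelled.** Baseline is then unused, and the interaction asks only whether the arms diverge after month 6. A benefit already present at month 6 and then maintained falls into the group main effect, which is not the stated test.

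At stake are the precision and, on the second reading, the meaning of the one analysis that covers the four follow-up visits jointly.

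**Working it through.** **Inputs (Statistical analysis).**
- Mean and SD: "taking a conservative baseline mean CVD risk score of 10.5% and a proportionate SD of 6" (both in percentage points).
- Difference: 20% × 10.5 = 2.1 points.
- Correlation: "assuming a correlation of 0.5 between baseline and follow up scores".
- Size: 152 per group, 304 in all; 304 / 0.85 = 358 to recruit.
- Significance level: the sample size uses 2.5% per primary outcome; the reporting rule is a p-"value of less than 0.05 (two-tailed) will be deemed to be statistically significant". Both levels are shown.

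**Assumptions not in the document.** The nurse effect is zero. For results over several visits, the correlation is 0.5 between every pair of visits (compound symmetry). Normal approximations are used throughout.

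**Step 1: the plan's own figure.** The sample size is described as being for the change score. SD of change = 6 × √(2 × (1 − 0.5)) = 6.0. At two-sided 2.5% and 80% power, n per group = 2 × 36 × (2.241 + 0.842)² / 2.1² = 155.2, so 156 per group and 312 in all, within 3% of 304. Power at 152 per group is 79.1%, so the stated 80% is reproduced for a change-score comparison. The baseline-adjusted SD, 6 × √(1 − 0.25) = 5.196, would give 117 per group, so adjustment was not built into the stated size.

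**Step 2: one visit against baseline, categorical time.**
- Unadjusted: SE = 6 × √(2/152) × √(2 × 0.5) = 0.688; 2.1 / 0.688 = 3.05.
- Adjusted: SE = 6 × √(2/152) × √(1 − 0.25) = 0.596; 2.1 / 0.596 = 3.52.

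| Two-sided level | Unadjusted power | Adjusted power | Gap (points) |
|---|---|---|---|
| 2.5% | 79.1% | 90.0% | 10.9 |
| 5% | 86.2% | 94.1% | 7.9 |

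The variance falls by 25%. In one simulated data set with baseline as an outcome, the interaction coefficient at a visit equalled the raw difference in change (−2.5836 both ways), which confirms the equivalence.

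**Step 3: sensitivity to the correlation (one visit, 2.5%).** At 0.3, power is 63.2% against 83.1%, a gap of about 20 points. At 0.7 it is 95.5% against 97.9%, a gap of about 2.

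**Step 4: joint test over the four follow-up visits (4 df, 2.5%).** Noncentrality = (152/2) × e′W⁻¹e. Here e holds the effects at the four visits. W is 18(I + J) for raw changes and 18(I + J/2) for baseline-adjusted values, with J the matrix of ones.

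| Shape of effect | Noncentrality | Unadjusted power | Adjusted power | Gap (points) |
|---|---|---|---|---|
| Constant 2.1 | 14.9 v 24.8 | 82.8% | 97.8% | 15.0 |
| Growing linearly to 2.1 at month 24 | 11.6 v 15.5 | 70.0% | 84.6% | 14.6 |
| 2.1 at month 12, fading to zero at month 24 | 13.0 v 15.5 | 76.1% | 84.6% | 8.5 |

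**Step 5: linear time, effect growing to 2.1 at month 24.** The slope difference is 2.1/24 = 0.0875 per month. Its SE is 0.0256 with a free group term and 0.0222 with a common baseline mean. Power at 2.5% is 87.9% against 95.5%.

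**Step 6: only months 6 to 24 modelled.** A constant 2.1-point benefit gives zero differences between follow-up visits, so the noncentrality is zero and the rejection probability equals the type I error rate (2.5%, or 5% at the looser level). For an effect growing linearly to 2.1, the joint interaction test has 39.4% power at 2.5%.

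**The case against.** The strongest defence has five parts.

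- **The primary analysis is already adjusted.** This stands. The regression for the primary outcomes contains baseline, and nothing makes the mixed model the deciding test of the hypotheses.
- **The planned power is met.** This stands too. The claim that the sample "provides 80% power to detect a relative change of 20% in 10-year CVD risk" was worked out for a change score, and 79.1% agrees with it. A reader might infer that the trial is underpowered by 11 points. The document does not support that: 90.0% is what adjustment would give, not what was promised.
- **Eleven points is not the loss in the planned test.** Correct. It is a single-visit figure at 2.5% and correlation 0.5. The planned test is an interaction over visits, and neither the coding of time nor the correlation between follow-ups is given. A score that includes age and gender may well be correlated above 0.5, which would shrink the gap.
- **No bias arises, and the models differ in other ways.** With baseline included and categorical time, the contrast is unbiased; chance imbalance adds variance only. Stratifying by age and gender limits that imbalance for the CVD score. A reader might also infer that any disagreement between the two models would come from the missing adjustment alone. It need not: they also differ in the visits used, in partly observed participants and in how nurse is handled.
- **A condensed article leaves detail to the analysis plan.** This holds for the coding of time. It does not answer the point, because the article lists the fixed effects and names the test. Followed as written, the model gives one of the two results above.

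**Conclusion.** The point holds as a weakness of the longitudinal analysis. If baseline is among the modelled timepoints, which the wording about assessing change suggests, precision is given away. At one visit this costs 10.9 power points at 2.5% or 7.9 at 5%, with correlation 0.5. At 2.5% the gap runs from about 20 points at correlation 0.3 to about 2 at 0.7. For the joint test it is about 8 to 15 points, depending on the shape of the effect and assuming compound symmetry. If only months 6 to 24 are modelled, the fault is a wrong contrast: a constant benefit cannot be detected through the interaction.

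It is not a shortfall from the stated 80% power, and it does not touch the primary regression. The figures are for the CVD risk score with no nurse effect. The document gives no comparable inputs for the SF-12, so the size of the loss there is not known, although the model has the same gap.

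**What to change.** State the role of baseline in the mixed model and use one of two forms, for the CVD risk score and the SF-12 scores alike:

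- **(a) Baseline as covariate.** Model months 6, 12, 18 and 24 as the outcome, with baseline score and baseline-by-time added to group, time and group-by-time. Report the group difference at each visit. Testing only the interaction would still miss a constant benefit.
- **(b) Baseline as outcome.** Keep all five timepoints and drop the group main effect, so that the arms share one baseline mean. With categorical time and baseline as reference, each group-by-time coefficient is then the group difference at that visit.

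The cost is a changed model statement and the matching change to the Stata call; no new data are needed. Option (a) drops any participant without a baseline score. Because baseline is measured before allocation, few should be lost, and option (b) avoids the loss.

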
### Data and trial monitoring

The study team responsible for the day to day running of the RCT comprise a trial manager, two clinical trial nurses, an administrate support worker, and a PhD student.

A study management committee, chaired by the project lead, with participation from study team members and consumer representatives will meet approximately 3-monthly to oversee the study and ensure effective data management. The committee will also report any adverse event to the South Australian Clinical Human Research Ethics Committee following standard procedures. They will also monitor interim analyses conducted by the statistician and will make the final decision regarding the appropriate stage to terminate the trial.

A national advisory panel of mental health and cardiovascular health experts, and national consumer advocates will meet 6-monthly to provide high level advice to the research group. A stakeholder working group of service managers, psychiatrists, GPs, care coordinators, other clinicians, and consumer advocates with lived experience of mental illness and physical health problems will confirm pathways and agree clinical protocols for mental health, primary care and community providers to ensure sustainability, execution and ongoing communication during the trial. Patients and carers will also be consulted through the Southern Adelaide Mental Health Consumer and Carer Advisory Group.

